## Abstract

**Background:**

Unfavorable lifestyle factors influence the risk of stress disorders. For risk reduction, lifestyle modifications, such as regular physical activity, balanced nutrition and competence in stress management, are a means of choice. The clinical study examines the efficacy of an intensive lifestyle intervention, named Individual Health Management (IHM), − with regard to a reduction of perceived stress. The study is supported by the major regional health insurance, which conducts, in cooperation with the Traditional Chinese Medicine (TCM) hospital, Bad Kötzting, a local model project offering insurants the IHM program as prevention measure against stress and related aftermath.

**Methods:**

The study is a controlled, randomized, monocentric trial with a 12-months intervention phase. Feasible persons are checked according to inclusion and exclusion criteria and assigned to the intervention or control group. Randomization ratio is 1:1. (A) Participants of the intervention group receive the lifestyle program IHM, have access to a web-based health portal (www.viterio.de), and join 3 full-day and 10 two-hour training sessions during the first 3 months. During the remaining 9 months, 4 training sessions and a weekly monitoring are performed with remote assistance. Besides measurement of perceived stress, examinations include burnout symptoms, heart rate variability, laboratory and physical findings. Further patient reported outcomes are documented (e.g. well-being, life satisfaction, severity of mood state, sense of coherence, psycho-vegetative test, cardio-metabolic risk factors, hypertension and diabetes risk. (B) Participants in the control group have access to the intensive lifestyle intervention IHM after a waiting period of at least 6 months. Examinations are conducted at baseline, after 3 and 6 months and in the intervention group additionally after 9 and 12 months. The confirmatory analysis examines the differences between the two groups with regard to changes in perceived stress after 6 months compared to the initial value.

**Discussion:**

In order to enhance adherence, avoid attrition and to insure data quality, different measures will be implemented in the study. Based on a blended learning concept including a web-based e-health tool named VITERIO®, the program promises to achieve sustainable effects in perceived stress.

**Trial registration:**

German Clinical Trial Register Freiburg (DRKS): DRKS00013040 (date registered 2017–10-1).

**Electronic supplementary material:**

The online version of this article (10.1186/s12889-018-5756-3) contains supplementary material, which is available to authorized users.

## Background

The subjective perception of excessive demands is discussed as causing a variety of diseases [1]. In this context chronic stress can lead to the development of a burnout syndrome [2] as well as overweight [3], high blood pressure [4] and diabetes [5]. For the indication “overweight”, the effects of lifestyle intervention on sustainable weight reduction (1 year and longer) are well documented in literature, like e.g. the “Look AHEAD” (action for health in diabetes) project [6] or “Guideline for the management of overweight and obesity in adults” [7]. Using the keyword “stress reduction” a literature search reveals predominantly studies, which concentrate their programs and techniques merely on the reduction of stress per se, rather than to change the whole life as practiced in intensive lifestyle intervention programs. In contrast a multimodal stress prevention program as executed in a very recently published randomized controlled study by Stier-Jarmer and coworkers, showed remarkably positive effects after 6 months in the intervention group as opposed to the control group [8]. A systematic review of 25 studies showed that 80% of all interventions had positive effects on burnout. The supply of refresher seminars intensified the success of the programs [9].

Main objective and target parameter of the study will be stress-reduction, although the basic concept of IHM (Individual Health Management) is very broad and multifaceted [10]. The sustainability of IHM has already been proven due to an all-embracing change in lifestyle [11, 12].

The stress prevention study is embedded into a comprehensive network program whose objective is to facilitate and to conduct prevention programs for different indications and risk groups at selected spa regions in Bavaria. Thereby the medical quality of health services offered in the spas shall be improved.

The study is supported by the major regional health insurance, AOK Bayern (Allgemeine Ortskrankenkasse - General Health Insurance, Bavaria), which conducts, in cooperation with the TCM hospital, Bad Kötzting, a local model project offering insurants the IHM program as preventive measure against stress and related aftermath. The outcomes are expected to have high impact on health policy, as the study is designed to provide evidence that perceived stress can be remarkably reduced already after 1 year of IHM lifestyle intervention. In case of positive outcomes a preventive effect on stress related diseases can be suggested, which will ultimately relieve health insurance providers.

In this context a randomized controlled trial on weight reduction (TALENT study) has been performed previously by our group [12, 13] resulting in a statistically significant weight reduction of about 10% of the baseline weight after one year [12]. Our own preliminary data showed our concept for a web-based lifestyle intervention program as applied throughout the IHM is a can be successfully implemented in a specialized spa region with suspected effectiveness in people with perceived stress [14]. The program has been conducted in the Bavarian health resort area of Bad Kötzting, which has become a center of preventive medicine – also due to the reason that the first German hospital for Traditional Chinese Medicine (TCM) is located there.

The comprehensive lifestyle intervention program IHM which has initially been established as a framework program for mainstream and complementary approaches of lifestyle medicine was developed at the Competence Center for Complementary Medicine and Naturopathy (CoCoNat) of the TU Munich, Germany. Basic medical experience, technical prerequisites and training resources necessary for the accomplishment of the IHM are on location. Development of the intensive lifestyle intervention was supported by public funding provided by the Bavarian Federal Health Office. By making use of both conventional and TCM methods, our comprehensive lifestyle intervention program addresses primarily all persons who would like to activate the body’s own resources and health supporting potential for self-healing [15].

The IHM should enable the participant to learn how to manage own stress situations through regulation of emotions. This should result in a reduction of the perceived stress levels.

Aim of the here presented study is to evaluate the efficacy of the lifestyle intervention program IHM in reduction of perceived stress in respect to a control group (waiting list) after 6 months. Additionally, within the IHM intervention group, the further course until the end of the lifestyle intervention program after 12 months will be analyzed.

## Methods

### Study design

The study is a monocentric randomized controlled trial. The study duration for each participant is 6 months. In the intervention group there is also a longitudinal analysis with examinations after months 9 and 12. The study will be performed at the SINOCUR prevention center in Bad Kötzting, Germany. The center is committed to be part of the core teams promoting Individual Health Management (IHM) which are pooled into a centrally coordinated network of health promotion called “IHM campus”.

### Web-based recruitment and participants

For recruitment of participants The AOK Bayern Health insurance contacted < 60.000 authorized insurants in the catchment area of the IHM Prevention center SINOCUR in Bad Kötzting, via written correspondence. The contacted persons are invited to conduct a short health survey in the e-Health portal VITERIO® which is part of the IHM [10]. At the end of the survey all interested persons can decide whether to take part in the study or not. The persons who are willing to participate in the study will contact the local IHM team in Bad Kötzting which will provide basic information around the study and perform the screening for the main inclusion criteria. A personal appointment with all persons who apparently will comply with the requirements of the study is planned and the trial physician will check all criteria for inclusion and exclusion after a comprehensive examination of all potential participants. Information on background, objectives benefits and risks of the study will be provided by the trial physician by a leaflet as well as orally.

### Inclusion/exclusion criteria

Persons of both sexes, aged 18–70 years resident in the catchment area of Bad Kötzting, with Tedium-Measure ≥3,20 (= moderate stress, pre-burnout), Perceived Stress Questionnaire (PSQ) total score > 41, and subjective feeling of stress exposure for more than 3 months, can be included in the study. A written informed consent is mandatory.

Persons will not be included if one of the following exclusion criteria is present: being unable to consent for themselves, insufficient skills in German language, no private access to internet, known hypertension (systolic blood pressure ≥ 160 mmHg or diastolic blood pressure ≥ 100 mmHg) with or without medication, known hypotension (systolic blood pressure ≤ 70 mmHg or diastolic blood pressure ≤ 50 mmHg), body mass index (BMI) < 17,5, psychiatric/psychotherapeutic treatment requirements defined as “severe signs and symptoms” according to the ISR (ICD-10-Symptom Rating) questionnaire in at least one of the subscales depressive syndrome, anxiety syndrome, obsessive-compulsive syndrome, somatoform syndrome, eating disorder syndrome or in the ISR total score, known psychiatric treatment (with or without medication), known diabetes mellitus (type 1 or 2), known heart disease (like CHD, arrhythmia, valvular heart defect, cardiac insufficiency), known gastric or duodenal ulcers, known diseases of the liver or kidneys, known diseases of the eyes (e.g. retinal detachment), known disease of the thyroid gland or taking of thyroid hormones, known disease-related impairments preventing a participation in the lifestyle program (e.g. arthrosis), known therapeutic conditions that are due to known risks/side effects not compatible with participation in the lifestyle program, known pregnancy (or lactation) or planned in the next year, participation in another currently clinical trial or during the last 6 months.

### Number of cases

Command variable was the change in overall perceived stress as evidenced by means of PSQ total score in month 6 in comparison to base line at month 0 (M0) collected as continuous numerical value.

For PSQ base line values over 41 mean reduction of overall PSQ levels after 6 months is expected to be 18 points in the intervention group and 9 points in the control group according to our own pilot study [14]. This corresponds to a 33% reduction of base line levels in the intervention group. Mean variation in PSQ value change was assumed to be 18 points in both groups. Therefore, the sample size for the t-test for independent groups (□ = 0.05, two-sided, power 80%, □ = 0.2) was estimated as 64 in each group (allocation ratio 1:1). Taking into account an expected dropout rate of 5%, a total sample size of 136 participants was deemed appropriate.

### Randomization

Randomization will be carried out as previously described by us [13]. Briefly, participants will be randomized after formal inclusion. Closed envelopes will be opened by the trial physician in strictly sequential order of the enrolments and the allocated study arm will be disclosed to the study participant. The allocation ratio is 1:1, means 1 for the intervention group and 1 for the control group (waiting list). Randomization will be prepared for 150 participants (including replacement numbers). An independent data manager at the institute for medical statistics and epidemiology at the TU Munich will prepare randomization and allocation envelopes.

### Intervention

The study compares an intervention (IHM = Individual Health Management) with a control group (6 months waiting list for IHM).

Group IHM: The lifestyle intervention program IHM is a therapeutic intervention against stress, pre-burnout and burnout. It consists of several phases and training packages and spans over a time period of 12 months, including intensive lifestyle counseling during the first three months. The basic training consists of an introduction phase with 3 health days and a training phase with ten weekly after-work group seminars. Subsequently the intervention program envisages a 9-months maintenance phase with weekly monitoring by specially trained health coaches and as needed distant lifestyle counseling, as well as trimestral refresher days (Fig. 1).

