### Statistical analysis

The confirmatory analysis will be conducted using a 2-sided significance test at the 5% significance level. Based on the intent-to-treat population (ITT) the primary outcome (change in perceived stress (PSQ total score) Δmonth 0 – month 6) will be tested by analysis of variance with the grouping factor “intervention” controlled for baseline value. In participants with missing data for PSQ total score at month 6 (drop-outs) an adequate conservative imputation technique will be applied. Secondary endpoints will be analyzed analogously but using an explorative approach.

All captured data will be analyzed descriptively by appropriate statistical parameters: absolute and relative frequencies for categorical data and arithmetic means, medians, standard deviations for numerical data. Where indicated, 95% confidence intervals will be presented. Apart from the confirmatory analysis a series of sensitivity analyses will be performed to explore the impact of different factors on the results of the analyses. Relevant factors are among others adherence to the protocol, adherence to the intervention program IHM and different responder definitions.

In terms of sensitivity analysis, primary and secondary endpoints will be examined based on the ITT as well as the per-protocol (PP) population. The ITT population will comprise all patients that had compiled the PSQ total score at least at baseline. They will be evaluated as randomized. Subjects will be considered PP if they had participated in the study according to the protocol.

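### Group seminars are given in the IHM arm only, but the sample size and confirmatory ANOVA assume independent participants, so the 5% error rate and 80% power are not assured if outcomes correlate within training groups

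*Protocol article*

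**What the plan says.** All references are to the Protocol article.

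- **Randomization:** individual participants, 1:1, in order of enrolment.
- **Intervention:** for the IHM arm, "The basic training consists of an introduction phase with 3 health days and a training phase with ten weekly after-work group seminars". A nine-month maintenance phase follows, with "weekly monitoring by specially trained health coaches". Controls are on a waiting list for six months, so they have no seminar group before the primary time point.
- **Number of cases:** the PSQ reduction at month 6 "is expected to be 18 points in the intervention group and 9 points in the control group". On spread, "Mean variation in PSQ value change was assumed to be 18 points in both groups". From these, "the sample size for the t-test for independent groups" gave 64 per group at 80% power, and 136 in total after 5% dropout. No design effect appears.
- **Statistical analysis:** "The confirmatory analysis will be conducted using a 2-sided significance test at the 5% significance level". The primary outcome "will be tested by analysis of variance with the grouping factor" intervention, controlled for the baseline value. There is no term for training group.
- **Sensitivity analyses:** those named are protocol adherence, programme adherence, responder definitions and ITT against PP. Quality assurance and bias adds a compliance score. Clustering is not among them.

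**The concern.** Individual randomisation with group teaching in one arm only is a partially nested design. People who take ten weekly sessions together may end up more alike on a self-reported stress score than people taught separately. The variance of the IHM arm mean is then larger than the SD divided by the square root of n would suggest, while the control arm is unaffected.

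A test that ignores this uses too small a standard error for the only confirmatory contrast. At stake are the error rate, the width of the confidence interval and the meaning of the 80%. The article also hopes to transfer the programme to other centres (Expected benefit), so the useful inference is about the programme given to new groups, and variation between groups belongs in the uncertainty.

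**Working it through.** **1. The plan's own figure.** Inputs from Number of cases: difference 18 − 9 = 9, SD 18, two-sided 0.05, power 80%.

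- Normal approximation: n = 2 × (1.96 + 0.84)² × 18² / 9² ≈ 62.7, so 63 per arm.
- Exact t-test: 63.77, so 64 per arm, with power 80.1%.
- Dropout: 64 / 0.95 = 67.4, so 68 per arm and 136 in total.

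The arithmetic is right under independence and leaves no margin for clustering.

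**2. Assumptions the article does not supply.** Analysed n = 64 per arm; 8 groups of 8 or 4 groups of 16; ICC of PSQ change in the IHM arm 0 to 0.10. The baseline covariate is left out because its correlation with change is not given.

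**3. Formulas.**

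- Design effect in the IHM arm: DE = 1 + (m − 1) × ICC. In controls it is 1.
- True SE = 18 × √((DE + 1)/64). SE under independence = 18 × √(2/64) = 3.18.
- Ratio R = √((DE + 1)/2).
- Type I error of the planned test ≈ 2 × (1 − Φ(1.96/R)).
- Power of an adjusted test: noncentral t with noncentrality 9/(true SE) and Satterthwaite df = (v₁ + v₂)² / (v₁²/(k − 1) + v₂²/63), where v₁ = 324 × DE/64, v₂ = 324/64 and k is the number of groups.

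Example with m = 16 and ICC 0.05: DE = 1 + 15 × 0.05 = 1.75. True SE = 18 × √(2.75/64) = 3.73. R = 3.73/3.18 = 1.173. Type I error = 2 × (1 − Φ(1.671)) ≈ 9.5%. Adjusted df ≈ 7.3 and adjusted power ≈ 55%.

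**4. Results.** The simulated columns apply the unadjusted two-sample t-test (200,000 simulated trials per cell for type I error, 100,000 for power).

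| Groups × size | ICC | DE | R | Type I, formula | Type I, simulated | Planned-test power, simulated | Adjusted-test power |
|---|---|---|---|---|---|---|---|
| 8 × 8 | 0 | 1.00 | 1.000 | 5.0% | 4.9% | 80% | 78% |
| 8 × 8 | 0.01 | 1.07 | 1.017 | 5.4% | 5.4% | 80% | 76% |
| 8 × 8 | 0.05 | 1.35 | 1.084 | 7.1% | 7.0% | 78% | 70% |
| 8 × 8 | 0.10 | 1.70 | 1.162 | 9.2% | 9.2% | 77% | 63% |
| 4 × 16 | 0 | 1.00 | 1.000 | 5.0% | 5.0% | 80% | 73% |
| 4 × 16 | 0.01 | 1.15 | 1.037 | 5.9% | 5.9% | 80% | 69% |
| 4 × 16 | 0.05 | 1.75 | 1.173 | 9.5% | 9.5% | 77% | 55% |
| 4 × 16 | 0.10 | 2.50 | 1.323 | 13.8% | 14.0% | 74% | 43% |

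With 5 to 6 groups, adjusted-test power is about 75 to 76% at ICC 0, 72 to 74% at 0.01 and 51 to 56% at 0.10.

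The interval suffers in the same way. At ICC 0.05 an unadjusted 95% interval covers about 100 − 7.0 = 93.0% (8 groups) to 100 − 9.5 = 90.5% (4 groups).

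**5. What the baseline covariate can do.** If baseline and change correlate at r, the variance shrinks by 1 − r². With m = 10 and ICC 0.02, DE = 1.18 and the variance rises by (1 + 1.18)/2 = 1.09, which r = √(1 − 1/1.09) = 0.29 offsets. With ICC 0.05, DE = 1.45, the factor is 1.225 and r = 0.43 is needed. This can restore precision. It does not correct the error rate, because the model still omits the group variance.

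**The case against.** **The size rests on values nobody has seen.** This stands. A reader might infer that the 5% and 80% simply do not hold. The article does not support that: it gives no ICC, group size or number of groups. At ICC 0 both figures hold for the planned test, and at ICC 0.01 with groups of 8 the shift is negligible.

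**The null matters.** This also stands. If IHM affects nobody, individual randomisation keeps the planned test near 5% whatever the grouping. Inflation needs a mean effect of zero with real group-level effects in both directions. The narrow confidence interval does not depend on that null; it arises whenever groups truly differ.

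**The planned test loses little power.** True: about 74 to 80% in the table. The marked loss is in an adjusted test, which the article does not plan.

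**The sources of clustering are easily overstated.** A reader might add joint attendance at the health days, shared coaches, or season. The article applies the word group only to the ten seminars. It does not say that seminar groups are fixed, gives no number of coaches, and describes coaching as review of each participant's own data. Season would reach concurrently enrolled controls as well.

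**A separate analysis plan may deal with it.** Possibly, and the list of sensitivity factors is open-ended. But the article itself names both the sample-size test and the confirmatory model, and both assume independence. A later group term would depart from that model and leave the 80% statement unchanged.

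**Conclusion.** The point holds in conditional form. The article describes group teaching in one arm and fixes a sample size and a confirmatory model that both ignore it. The mismatch is certain; its consequence is not.

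Over the assumed range, the excess type I error runs from under one percentage point (ICC 0.01) to about nine (ICC 0.10 with four groups), for a zero mean effect with between-group variation. The error rate and the interval are the stronger part of the argument. The power part is weaker: it concerns mainly an adjusted test, and baseline adjustment may recover some of the loss.

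**What to change.** 1. Record the training group of each IHM participant as the seminars are delivered. If this is lost, no later correction is possible.
2. Analyse the primary endpoint with a partially nested model: PSQ change on arm and baseline PSQ, a random training-group effect in the IHM arm only, and small-sample degrees of freedom (Satterthwaite or Kenward-Roger). Make this the confirmatory analysis or, at minimum, a prespecified sensitivity analysis reported beside the ANOVA.
3. In Number of cases, state that 80% assumes no within-group correlation and the unadjusted t-test. Add the planned group size and number of groups, and give power over an ICC range using the degrees of freedom of the adjusted test. Figures based on 126 degrees of freedom would be too favourable: with m = 12 they run from about 78% at ICC 0.01 to 62% at ICC 0.10, against about 73% and 53% with Satterthwaite degrees of freedom.

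Cost: one identifier and some wording, with no additional participants. The price is a wider confidence interval, a less favourable stated power and, with few groups, an imprecise estimate of the group variance. That last point is a fair reason to prefer the sensitivity-analysis option if only four or five groups are planned.

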**Fig. 1 Fig1:**
[figure not shown]
Course of action intervention group

In particular the introduction phase consists of three full health days in which the participants learn how to practice self-awareness (individual life conditions and their impact on the health status), how to optimize quality of life and life satisfaction as well as the proper TCM constitution type. The participants are trained how to use the e-Health portal VITERIO® and how to perform 6-min- and 2-km-walking-tests and basic knowledge on “3–1-2” QiGong relaxation technique among others. Further training contents are techniques of time management, information on stress and resilience, regulation of mood and exertion, the significance of dietary days for stress reduction, knowledge of the individual risk and protection factors, and to determine individual aims in life.

During the intervals of the three health days, participants are encouraged to perform self-observation and to document their lifestyle in the VITERIO® e-Health portal, which performs an evaluation in form of a so-called time-and-mood analysis. The results shall enhance the participant’s sense of self. Additionally health behavior in regard to movement, nutrition and stress will be promoted. By means of systematic feedback to VITERIO® the participants’ changes in lifestyle, behavior and regulation of emotions will be recorded and evaluated.

The 3-month-training-phase encompasses 10, not less than 2-h after work training sessions in which the participant practices health behavior, in particular mental resilience and handling of stress, relaxation techniques, and how to plan “being and staying healthy” with medical check-ups and priority lists. There will be lectures on time management, nutrition and deeper insights into QiGong.

During the subsequent 9-month-maintenance phase, the participants are monitored on a weekly base by the health coaches. Via a PROFI (provider reported outcomes of findings and interventions) access to VITERIO® the Coach has insight into the individual health data entered by the participant into the e-health portal. Thereby changes in perceived stress or weight can be detected and analyzed in depth. On demand this type of distant life style counseling can be supplemented by personal training sessions. 4 refresher sessions within 9 months shall be performed in order to deepen and substantiate teaching and learning contents.

Based on the documented health data, the health coach provides a final assessment that reveals the achievement of the participant’s goals at the end of the intervention.

Figure 2 shows the basic design of the study with the two study groups. Table 1 gives an overview on the study process.

